### Sample size and power

The total of 2,400 respondents will allow us to detect changes between current intervention and control sites in resource use across the spectrum of risk. For example we shall have 80% power when using a 5% significance level to detect changes of 15% in the proportion of patients at a defined risk receiving a specified resource, such as case management or support to quit smoking.

### Analysis

The study will comply with the Statistics Standard Operating Procedure (SOP) of the West Wales Organisation for Rigorous Trials in Health (WWORTH), the clinical trials unit at Swansea University. Primary analysis will be by treatment allocated. The primary outcomes are number of emergency admissions per patient and the time to first event (namely emergency admission). The first of these is a count variable and hence can be modelled using a generalised linear model incorporating an appropriate discrete distribution; the second is a measurement variable, subject to right-censoring, and can be modelled using appropriate survival analysis techniques including Cox’s proportional hazards models. Both methods take account of covariates and explanatory factors (including whether the participant’s practice has yet adopted Prism or not); neither methodology makes any normality assumptions. The list of potential explanatory factors and covariates includes baseline observations, time-varying covariates and days at risk.

The technical performance of the Prism tool will be assessed by analysing the data at baseline and across the control phase. We will plot the proportion of patients who experience hospital admissions against the prospective Prism risk score and calculate sensitivity, specificity, positive and negative predictive values. We will control for any confounding effects of Prism implementation during the analysis period by fitting a binary parameter showing whether practices have adopted Prism yet or not.

The perspective of NHS Wales and personal social services will be adopted for the health economic analysis. The costs of implementing Prism in intervention and control sites will be derived from interviews with GP practice staff and with members of the main trial team (e.g. training resources). The costs associated with resulting changes in care processes will be derived from routine data collected by the Prism system from SAIL and by patient-reported information collected by the CSRI questionnaire. Costs will be presented in a tabular format reporting the estimated resource quantities and unit costs attached. The estimation of the size of the differences (means and standard deviations) in resource use between intervention and control sites within each of the four risk strata and overall will be calculated and valued in monetary terms using published unit costs (with year of reported cost reported) [36]. The primary health economic analysis will be the calculation of the incremental cost per emergency admission avoided in a cost-effectiveness analysis and will produce a tabular representation of costs versus changes in primary and secondary outcomes in a cost-consequences analysis. The incremental cost per quality-adjusted life year (cost/QALY) will be calculated in a cost-utility analysis using SF-6D utility scores derived from SF-12 patient questionnaire data. A series of univariate sensitivity analyses will be carried out to determine the extent to which changes in the basic assumptions of the economic analysis affect the incremental cost-effectiveness ratio.

We will record and transcribe focus groups and interviews and analyse them thematically. This is a systematic and transparent method of analysis that generates themes from the explicit and implicit ideas contained in the original accounts of participants. One researcher will lead the analysis with two others independently supporting key stages of coding, generating themes and interpretation and encouraging a critical stance to test and confirm findings [35,37,38].

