Although condition-specific risk prediction tools have been successfully developed and applied to conditions such as diabetes and coronary heart disease [17,18], there is less evidence regarding generic population-based tools. Predictive models, such as Patients at Risk of Readmission (PARR) and Scottish Patients At Risk of Readmission and Admission (SPARRA), have been used successfully in the UK National Health Service (NHS) to stratify patients into risk levels [19,20]. The models used in England and Scotland focussed only on those at most risk – on patients over 65 years in Scotland and on the sickest 1% or 2% in England. Steps to include the whole population were later included in the English Combined Predictive Model and are now being taken in Wales through the development of a predictive risk stratification model (Prism) [21]. Prism calculates a risk score of between 0 (no risk) and 100 (very high risk), based on patient demographics and data from primary and secondary care record systems. Patients are stratified into four levels based on their individual risk of having an emergency admission to hospital during the following year. This reflects the Welsh Chronic Conditions Management policy focus to prevent disease onset and deterioration across the population [6]. The performance of Prism appears comparable to or better than the English model [21] and an independent pilot evaluation [22] has indicated potential for impact. However, many practical questions remain about how it will be adopted and used by service providers for each risk stratum [23].

Although stratification will not in itself lead to improvements in service delivery, it aims to stimulate the planning and targeting of care. Thus it is intended to influence health care delivery and ultimately patient outcomes. Recent policy documents in the UK and internationally have generated expectations that, in future, health communities will routinely stratify their populations according to risk of hospital admission [1,2,6,24,25]. To inform future policy and practice we designed a prospective evaluation of the implementation of Prism and present the study protocol in this article.

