### Prism

Prism is a web-based predictive risk tool commissioned by the Welsh Government that stratifies a General Practice population into four levels based on the individual risk of an emergency admission to hospital in the following 12 months. Prism was developed and checked using 300,000 (10% of the Welsh population) anonymised GP and hospital records from which 37 variables with the highest predictive power were selected. The variables used to develop Prism were drawn from routinely available data on inpatient, outpatient and primary care episodes and from the Welsh Index of Multiple Deprivation (http://wales.gov.uk/topics/statistics/theme/wimd/wimdstatement/;jsessionid=36B68DFE653760993E3E03966D7760B8?lang=en), which includes data on employment, income, housing, environment, education and health. To enable GP practices, individually or collectively, to plan workforce and resource allocation, each stratum represents a variable percentage of the practice population (which can be changed at the practice level depending on how they want to look at their own population data) with the top stratum (level 4) of patients being at highest risk of an emergency admission in the following year. The theoretical basis of the model is that patients in each of the four strata need very different targeted resources: level 4 requires individual case management, level 3 requires disease management on a population basis, level 2 requires supported self-care and level 1 needs prevention of illness and promotion of health and wellbeing.

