#### Focus groups and interviews

We will collect qualitative data from GPs and practice staff at baseline and post implementation to explore current practice in chronic conditions management and processes of change initiated by Prism. Questions will address attitudes, expectations and experience relating to predictive risk stratification and specifically the Prism tool, including barriers and facilitators to use.

At baseline, before Prism is activated in the first intervention practices we will conduct four focus groups with staff from general practices, two in one locality where geography suggests a natural division and one each in the other two locality areas. GPs unable to take part in a focus group will be offered an interview by telephone or face-to-face. We will also conduct focus groups with area-wide senior managers and community-based practitioners, one at baseline and one at the end of the intervention period. Focus groups will allow exploration of different views and experiences and encourage group interaction [34].

In order to gain more in-depth information about adoption and use and perceptions of effectiveness, we will undertake one-to-one interviews with staff following Prism implementation. We will purposively sample half the participating practices (20, based on 40 participating practices) and interview Prism user(s) at two time points—3 and 9 months after Prism implementation—face-to-face or by telephone. This will allow us to explore changes in adoption and use over time. We will administer a questionnaire to the other half of participating practices, also at 3 and 9 months but before interviews take place. Questionnaire responses will inform our interviews and enable us to see divergence or concurrence across all participating practices.

We will also interview three senior managers within ABM UHB during implementation to explore area-wide issues related to patient management and the effects of Prism in GP practices. Interviews will allow us to explore in detail respondents’ views about Prism and the use of the tool in their area [35].

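### The one intervention term named for the primary models is a yes/no switch, which under-reports a lagged effect when calendar time is modelled; an analysis by time since go-live should be prespecified beside it

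*Protocol article*

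**What the plan says.** The Design section describes a stepped wedge: all practices start as controls and go live at randomised, staggered times. The Analysis section proposes a generalised linear model for the number of emergency admissions and survival models for time to first admission. Both take account of covariates and explanatory factors, among them whether the participant's "practice has yet adopted Prism or not". The potential covariates are given as "baseline observations, time-varying covariates and days at risk". The analysis principle is "Primary analysis will be by treatment allocated". For technical performance, the same section speaks of "fitting a binary parameter showing whether practices have adopted Prism yet or not". Neither time since go-live nor calendar period is named.

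Two other places bear on how quickly an effect could appear. The Background says: "Although stratification will not in itself lead to improvements in service delivery, it aims to stimulate the planning and targeting of care". Under Focus groups and interviews, users in half the practices are interviewed 3 and 9 months after implementation, and the reason given is: "This will allow us to explore changes in adoption and use over time".

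**The concern.** A yes/no term describes an effect that arrives in full at go-live and then stays level. If Prism works by changing how practices plan and target care, some delay before admissions change is plausible.

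With staggered go-live and calendar terms in the model, delay does more than dilute the estimate. Practices already exposed act as comparators for those just switching. While their effect is still rising, the calendar terms absorb part of that rise, and the newly exposed practices are judged against it. The switch estimate can then fall well below the average effect that practices actually experienced.

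The problem is the same whether the switch is coded by allocated or by actual go-live. At stake is the main answer on emergency admissions, and with it the primary economic result, the cost per admission avoided. A near-null switch estimate could mean no effect or an effect that builds up.

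**Working it through.** The protocol gives no figure for this point. Its one power statement concerns questionnaire proportions and does not bear on it.

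**Inputs from the protocol:** 11 practice clusters (Design), and 18 months from first go-live as the last data point (Postal questionnaires).

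**Assumed, because the text does not give them:** one go-live date per cluster, spread evenly over 6, 9 or 12 months and rounded to whole months; 6 months of prior data; monthly cluster means of 1,000 patients; intracluster correlation 0.01; cluster autocorrelation 0.9; fixed month effects.

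**Formulas**
- Effect at s months since go-live, as a share of the full effect: f(s) = min(s/L, 1), with L = 3, 6 or 12 months and s taken at mid-month.
- True average: the sum of f(s) over exposed cluster-months, divided by their number.
- Switch estimate: the intervention element of (ΣD′V⁻¹D)⁻¹ ΣD′V⁻¹y. D holds the month indicators and the switch, and y holds f(s). V has 0.01 + 0.99/1000 on the diagonal and 0.01 × 0.9 = 0.009 off it.

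**Hand check of the true average.** With a 6-month roll-out, the 11 go-live months are 0, 1, 1, 2, 2, 3, 4, 4, 5, 5, 6, which sum to 33. Exposed cluster-months are 11 × 18 − 33 = 165. A ramp of length L loses L/2 months of full effect per cluster. For L = 6 the average is 1 − (11 × 3)/165 = 0.80. For L = 12 it is 1 − (11 × 6)/165 = 0.60.

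**Results with month effects (share of full effect; roll-out 6 / 9 / 12 months)**

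| Ramp | Switch estimate | True average | Kept by switch |
|---|---|---|---|
| Immediate | 1.00 / 1.00 / 1.00 | 1.00 / 1.00 / 1.00 | 100% |
| 3 months | 0.42 / 0.53 / 0.61 | 0.90 / 0.89 / 0.88 | 47% / 59% / 69% |
| 6 months | 0.16 / 0.24 / 0.32 | 0.80 / 0.78 / 0.75 | 20% / 31% / 43% |
| 12 months | 0.00 / 0.01 / 0.04 | 0.60 / 0.56 / 0.53 | 0% / 2% / 8% |

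**Without month effects**, in the same layouts, the switch returns 0.72-0.79 for a 6-month ramp (true 0.75-0.80) and 0.48-0.59 for a 12-month ramp (true 0.53-0.60). It is then close to the truth, but any secular trend in admissions is confounded with Prism.

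**Other layouts** (4 or 11 sequences, other step lengths and correlations, with period and cluster effects): a 6-month ramp keeps 28-54% and a 12-month ramp between −3% and 26%. Three monthly steps keep only 15-17% of a 6-month ramp.

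**Poisson check** (32 practices of about 600,000/77 ≈ 7,800 patients; assumed 0.8% admitted per month, final rate ratio 0.80, period and practice effects). For a 12-month ramp, the true average rate ratio is 0.856 and the switch reports 0.975, about 17% kept on the log scale. For a 6-month ramp the figures are 0.825 and 0.915, about 46% kept.

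**What bands of time since go-live recover** (first set-up, 12-month ramp): four bands (0-3, 3-6, 6-9, 9+ months) return 0.36-0.45 against a true 0.53-0.60. The standard error of the exposure-weighted average, relative to the switch, is 1.63 / 1.49 / 1.32 with four bands and 1.48 / 1.35 / 1.24 with three (0-3, 3-6, 6+).

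**The case against.** The strongest reply is that the article fixes less than the calculation assumes. The switch appears in a parenthesis that begins with the word including, and the list of potential covariates has room for a time-since-go-live term. The explicit mention of a binary parameter belongs to the technical-performance analysis. Exposure coding is commonly settled in an analysis plan. All of this limits how firmly the point can be put. It remains true that the only intervention term named for the primary models is a switch.

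Three stronger readings are tempting, and the document does not support them.

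- A reader might infer that the protocol expects use to build up. It says only that changes will be explored, and decay after initial enthusiasm would fit equally well. The 12 months in "individual risk of an emergency admission to hospital in the following 12 months" is the score's prediction window, not a lag in the intervention. Training is arranged before implementation, so it is not part of a lag either.
- A reader might infer that the primary result will come out near zero or with the wrong sign. Near zero needs slow growth together with calendar and cluster terms, and the article names no calendar term. Slightly negative values appear only in some of the other layouts. Omitting calendar time is no real escape, however, because trend is then confounded with Prism, and a linear calendar trend brings the loss back.
- A reader might infer that the switch must give way as the primary model. That is a trade-off between bias and variance. If the effect is immediate and constant, the switch is unbiased and more precise, and bands still understate a slow ramp.

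**Conclusion.** The point holds as a case for a prespecified companion analysis. It does not show that the named model is wrong. A switch assumes an immediate, constant effect, which sits uneasily with the indirect route the protocol describes. How much is lost depends on a speed of change that the protocol does not state: roughly a third to a half of the true average for a 3-month build-up, 57-80% for 6 months, and nearly all for 12 months. Nothing is lost if the effect is immediate and constant. These sizes rest on the assumed roll-out, linear ramps, correlations, and calendar-period and cluster terms in the model. The direction holds across every layout with calendar and cluster terms that was tried. It is a cheap improvement, and it is best made before results are seen, since adding it after a null finding would look post hoc.

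**What to change.** Keep the switch model. Beside it, with calendar period in both, prespecify a model with bands of time since the practice's randomised go-live, for example 0-3, 3-6, 6-9 and 9+ months. Report the effect in each band and the exposure-weighted average. State that a near-null switch estimate alone will not be read as no effect. State also that effects at exposure times longer than the roll-out have no unexposed concurrent comparator, so they lean on the model.

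The cost is a few model terms built from go-live dates that the trial already holds. The averaged effect is less precise: its standard error is about 32-63% larger with four bands and 24-48% larger with three. Bands recover a 12-month ramp only in part, so the write-up should not present the banded average as free of bias. Monthly exposure indicators recovered the full average in the layouts tested, but with a standard error 1.4 to 2.3 times that of the switch.

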**Methods/Design:**

We will undertake a mixed methods progressive cluster-randomised trial. Practices begin as controls, delivering usual care without Prism. Practices will receive Prism and training randomly, and thereafter be able to use Prism with clinical and technical support. We will compare costs, processes of care, satisfaction and patient outcomes at baseline, 6 and 18 months, using routine data and postal questionnaires. We will assess technical performance by comparing predicted against actual emergency admissions. Focus groups and interviews will be undertaken to understand how Prism is perceived and adopted by practitioners and policy makers. We will model data using generalised linear models and survival analysis techniques to determine whether any differences exist between intervention and control groups. We will take account of covariates and explanatory factors. In the economic evaluation we will carry out a cost-effectiveness analysis to examine incremental cost per emergency admission to hospital avoided and will examine costs versus changes in primary and secondary outcomes in a cost-consequence analysis. We will also examine changes in quality of life of patients across the risk spectrum. We will record and transcribe focus groups and interviews and analyse them thematically. We have received full ethical and R&D approvals for the study and Information Governance Review Panel (IGRP) permission for the use of routine data. We will comply with the CONSORT guidelines and will disseminate the findings at national and international conferences and in peer-reviewed journals.

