### Design

We will undertake a mixed-methods progressive cluster-randomised trial with a quantitative evaluation sited within an area in southwest Wales and qualitative fieldwork across the whole of Wales. The main trial site, Abertawe Bro Morgannwg University Health Board (ABM UHB), is the second largest of seven health boards in Wales, serving around 600,000 people. It is divided into 11 GP practice clusters, within which there are 77 general practices. We will invite each of these practices to participate, with a target of 30–40 recruited practices.

The study fulfils the last of the three major steps (that of evaluating the clinical performance), in researching multivariable prognostic models identified by the recent series in the British Medical Journal [9].

So that all participating practices have the opportunity to implement and use the Prism tool during the study period, we will use a progressive cluster-randomised trial design (randomised multiple interrupted time-series or stepped wedge design) [26-28] (see Figure 1).

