**Figure 1 F1:**
[figure not shown]
Randomised multiple interrupted time-series study design overview.

All participating practices will begin as control practices without Prism; receive the Prism package and training; and thereafter be able to use Prism with clinical and technical support. Randomisation of practice clusters will be stratified by locality. The West Wales Organisation for Rigorous Trials in Health (WWORTH) will produce a random allocation schedule for the trial. Allocations will be concealed from the practices until 6 weeks prior to receiving the intervention. They will then be notified of the timescale for receipt of the intervention by telephone and email and training will be arranged before implementation of the intervention.

As the trial progresses, the number of intervention practices will increase and the number of control practices will fall. This design protects against many sources of bias, including inherent differences in study sites, contamination between practices, arbitrary changes in health policy and the ‘resentful demoralisation’ of controls deprived of the intervention.

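### The primary models, as the article states them, name neither the randomised unit nor calendar period, although the trial is a stepped wedge randomised by practice cluster

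*Protocol article*

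**What the plan says.** Under Design, the article describes a "progressive cluster-randomised trial design (randomised multiple interrupted time-series or stepped wedge design"). The text beside Figure 1 adds that "Randomisation of practice clusters will be stratified by locality" and claims: "This design protects against many sources of bias, including inherent differences in study sites"; changes in health policy are on the same list of biases. The health board area is described thus: "It is divided into 11 GP practice clusters, within which there are 77 general practices", "with a target of 30–40 recruited practices". The Abstract, by contrast, speaks of practices receiving Prism at random.

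Under Analysis, the count of emergency admissions "can be modelled using a generalised linear model incorporating an appropriate discrete distribution". Time to first admission is to be handled by survival techniques, Cox among them. Both may include a term for whether the patient's practice has adopted Prism yet. On the remaining terms: "The list of potential explanatory factors and covariates includes baseline observations, time-varying covariates and days at risk". The section remarks that neither approach assumes normality and does not mention independence. It says that the primary analysis is by treatment allocated and refers to the trials unit's statistics procedure, which is not shown.

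Neither the Analysis nor the Sample size section mentions a practice, cluster, locality or period effect, an intracluster correlation (ICC), a random effect, a frailty or a robust variance.

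**The concern.** A stepped wedge has two features that its analysis must respect. Patients in one practice share an admission rate that differs from other practices, and allocation is by site, so the number of sites limits the precision. And every site moves from control to Prism, so exposure is correlated with calendar time. The protection claimed against site differences and policy change comes from fitting site and time; random timing alone does not supply it.

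The primary data cover every registered patient who does not dissent. If these patients are analysed as independent, ordinary differences between practices can look significant. If time is left out, a drift in emergency admissions is read as an effect of Prism. The cost per emergency admission avoided, which is the main economic result, would inherit both errors.

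**Working it through.** **The plan's own figure.** The only power statement (80% at 5% significance for a 15% change, 2,400 respondents) concerns a survey proportion. It reproduces if 15% means percentage points centred on 50% (42.5% v 57.5%) in the smallest risk stratum: 15% of 2,400 = 360, or 180 per condition.

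- Null SE = √(2 × 0.25/180) = 0.0527; alternative SE = √(2 × 0.425 × 0.575/180) = 0.0521.
- Power = Φ((0.15 − 1.96 × 0.0527)/0.0521) = Φ(0.90) = 0.815.

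That is a calculation with independent respondents. With 360/40 = 9 per practice and design effect 1 + 8 × ICC, assumed ICCs of 0.01, 0.05 and 0.10 give power of 0.785, 0.674 and 0.565. The planning text therefore shows no allowance for clustering either. No power or ICC is given for the primary outcomes.

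**Primary count model: inputs.** From the article: 32 practices recruited and 600,000/77 = 7,792 patients per practice if lists are equal, so 32 × 7,792 ≈ 249,000 patients. Assumed, because the article does not give them: 0.1 admissions per patient-year, 24 monthly periods, roll-out from month 4 to month 18, between-practice CV of 0.1 to 0.3, and a log-rate trend of 0 or 0.03 per year.

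**Method.** Expected admissions per practice-month are μ = 7,792 × 0.1/12 = 64.9. For a design matrix D, the model-based variance is (D′D)⁻¹/μ. The true variance is (D′D)⁻¹D′VD(D′D)⁻¹, where V adds the shared practice variance CV² to the Poisson part 1/μ.

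For the Prism term alone, with 32 × 24 = 768 cells of which 54% are under Prism:

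- Model SE = 1/√(64.9 × 768 × 0.54 × 0.46) = 0.009.
- True variance = 0.009² + 0.0156 × CV² in this layout.
- Type I error with no trend = 2Φ(−1.96/ratio), where ratio = true SE/model SE.

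| Terms fitted | CV | Model SE | True SE | Ratio | Type I error, no trend |
|---|---|---|---|---|---|
| Prism only | 0.1 | 0.009 | 0.015 | 1.7 | 25% |
| Prism only | 0.2 | 0.009 | 0.027 | 3.0 | 51% |
| Prism only | 0.3 | 0.009 | 0.039 | 4.3 | 65% |
| Prism + period | 0.1 to 0.3 | 0.014 | 0.034 to 0.093 | 2.4 to 6.6 | 41% to 77% |
| Prism + period + practice | 0.1 to 0.3 | 0.017 | 0.017 | 1.0 | 5% |

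If 10% of the practice variance is practice-by-period, the last row becomes 6% to 12%, so fixed practice effects alone are not quite enough.

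**Trend.** With a log trend of 0.03 per year, the Prism-only model is biased by +0.026 (rate ratio e^0.026 ≈ 1.03), which is 0.0263/0.03 = 88% of one year's trend. It rejects a true null in 68% to 72% of trials. Adding period removes the bias.

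**Low practice variation.** At CV 0.05, true SE = √(0.000081 + 0.0156 × 0.0025) = 0.011, the ratio is 1.22 and type I error is 2Φ(−1.61) ≈ 11%. The trend bias is unchanged: rejection is about Φ((0.0263 − 1.96 × 0.009)/0.011) ≈ 79%.

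**Unit randomised.** If the 11 practice clusters are the unit (CV 0.1 between clusters), the Prism-only ratio is 2.7 and type I error is 47%. With period and cluster terms it is 5% by the normal approximation, which is optimistic for 11 units.

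**Second layout.** A separate set of 300 simulated null trials assumed 18 months, roll-out over months 1 to 8, practice SD of log rate 0.15 and practice-month SD 0.05. With no trend, the Prism-only Poisson model rejected in 29%, falling to 7% with practice SD 0.05 and practice-month SD 0.02. Practice and month effects with practice-clustered standard errors gave 5% to 6%.

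**The case against.** The strongest reply is that the article commits to no such model. Its verb is permissive, its list is of potential terms and is open, and a generalised linear or Cox framework admits random effects, robust variances and frailty. A statistics procedure and fuller analysis plans exist or may exist. That stands: a reader might infer that the trial will ignore clustering and time, and the document does not say so.

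Other stronger readings also fail:

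- **Calendar time is certainly excluded.** Not shown; time-varying covariates could include it.
- **Cox is biased by trend.** Not in general. If time runs from a common trial start with Prism status time-varying, the baseline hazard absorbs the trend. The time scale is not stated.
- **Standard errors are too small 3.0 to 6.3 fold.** That follows from 1 + (m − 1) × ICC at ICCs of 0.001 and 0.005, a formula for parallel groups. Here each practice supplies both control and Prism time, so it exaggerates.
- **Days at risk is misused as a covariate.** The loose list is compatible with an offset.
- **The primary analysis is a snapshot.** The Abstract says "We will compare costs, processes of care, satisfaction and patient outcomes at baseline, 6 and 18 months", but Table 1 gives these as collection times and the Methods describe a continuous process.

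What the reply does not meet is that the section is specific enough to name the exposure term and days at risk, yet omits the two features that define this design, while the design text claims the protection that only those features provide.

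**Conclusion.** The point holds as a defect in the stated model. The article gives model families, exposure and candidate terms that do not match its own randomisation, and it leaves unclear whether the practice or the practice cluster is the unit.

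If only the named terms were fitted and calendar time were not among them, the count analysis would understate the standard error by about 1.7 to 4.3 fold at an assumed CV of 0.1 to 0.3 (about 1.2 fold at 0.05) and would carry most of one year's trend into the Prism effect. If calendar time is among the covariates, the trend bias goes but the standard error is still too small. For Cox, the clustering error applies on any time scale.

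The direction is secure. The size rests on an admission rate, practice variation, trend and roll-out that the article does not give. Results for 40 practices are almost the same.

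**What to change.** State for each primary outcome how the design enters the model:

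- **Unit.** Say whether the practice or the practice cluster is randomised, and use the same term throughout.
- **Count model.** Fixed calendar-period (or step) effects; locality; a random effect or cluster-robust variance for the unit randomised; small-sample inference based on the number of such units; log(days at risk) as offset. If fixed or random practice effects are used alone, allow for practice-by-period variation.
- **Cox model.** Calendar time from a common start as the time scale, allocated Prism status as a time-varying term (in line with the stated analysis by treatment allocated), and cluster-robust variance or frailty for the same unit.

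The cost is wording and slightly more analysis work; no new data are needed. Confidence intervals widen. In the assumed layout, the standard error with period and practice fitted is 0.017, against the 0.009 that the Prism-only model would report: 0.0169/0.009 ≈ 1.9 times as wide. The narrower interval was never valid, so little real precision is lost. This should be settled before the outcome data are analysed.
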